## Abstract

Background: Stroke survivors experience significant alterations in their daily functionality that has a negative impact on their functionality, participation, and quality of life. Person-centered approaches in Physical Therapy interventions that are focused on functional and meaningful goals help to minimize the impact of the alterations. Therefore, the aim of this study is to assess the effectiveness of a Physical Therapy intervention based on a goal-oriented approach with task-specific training for improving functionality, participation, and quality of life for people with Stroke. Methods: A single-blinded randomized controlled clinical trial will be developed. Adults over 50 years old diagnosed with Stroke over 6 months will be included in this study. Participants (n = 62) will be randomly allocated into two groups: The experimental group (n = 31) will receive 30 sessions, three per week during 10 weeks, of Physical Therapy sessions of goal-directed and task-specific training. The control group (n = 31) will follow the same intervention intensity of their usual Physical Therapy treatment. The primary outcome variables quality of life (NewsQol), participation (Ox-PAQ), and gait functionality (FAC) and the secondary outcome variables functional disability (BI), postural control (PASS), dynamic trunk balance (TIS), and functional goals (GAS) will be measured at baseline, after group interventions (10 weeks), and 6 months after the baseline. Statistical analyses will include repeated-measures ANOVA, Student’s *t*-test, or the Mann–Whitney U-test, with a 95% confidence interval and significance level of *p* < 0.05. Conclusion: Person-centered approaches in Physical Therapy interventions may yield better outcomes in functionality, participation, and quality of life for Stroke patients compared to standardized interventions. Trial registration: ClinicalTrials.gov: NCT06165666 (December 2023).

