Therefore, the aim of this study is to assess the effectiveness of a PT intervention based on goal-oriented approaches and task-specific training for improving functionality, participation, and quality of life for people with Stroke.

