### 2.3. Sample Size Calculation

Sample size was calculated using G*Power software 3.1.9.7© (Germany) [30]. In order to detect differences in quality of life in favor of the EG, a large effect size of d = 0.80, an error α = 0.05, and a power of 90% were assumed. Considering a possible loss to follow-up of 10%, the sample size results in 62 participants.

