### 2.7. Outcome Variables

Outcome variables will be collected at 3 points: at baseline (A0), at the end of the group interventions (A1), and 6 months after baseline (A2). The assessments will be carried out by 2 Physical Therapists, members of the research team, after training and consensus meetings. The assignment will be blinded to the two physical therapist assessors. Sociodemographic variables (Table 1) are age, sex, duration of Stroke, work status, type of Stroke, affected hemibody and comorbidities.

*Primary variables* (Table 2) are as follows:-Quality of Life: Measured with the Spanish version of Newcastle Stroke-Specific Quality of Life Measure (NewsQoL), developed by Buck et al. [32] to measure the quality of life of people after a Stroke. It consists of 56 items distributed in 11 dimensions. The range of scores varies from 0 to 3 points for each of the items. In each dimension, a result is obtained from 0% to 100%, with a higher score representing a worse perception of quality of life. It is adapted and validated in the Spanish population [33] and it has proven to be sensitive and reliable [34].-Participation: Measured with the Oxford Participation and Activities Questionnaire (Ox-PAQ), an instrument for measuring participation and activity levels based on the International Classification of Functioning, Disability and Health (ICF) [35]. It consists of 23 items divided into 3 dimensions: routine activities, social commitment, and emotional well-being. Each item is scored on a Likert scale from 0 to 4 points. Higher results mean greater difficulty in participation [35]. It is valid for people who have suffered a Stroke [36], and the Spanish version is up to be done.-Functionality: Measured with the modified Barthel Index [37], used to assess the functionality of activities of daily living of people with neuromuscular and/or musculoskeletal pathology, especially in those who have suffered Stroke. The total score ranges from 0 to 100, where 0 indicates complete dependence and 100 indicates complete independence. It is cross-culturally adapted and validated in the Spanish population [38].

**Table 2 jpm-14-00891-t002:** Outcome variables.

Outcome Variables	Assessment Period			Measuring Instruments
	Baseline	Post-Treatment	Six Months after Baseline	
Perception of Quality of Life	x	x	x	NewsQoL-S.V.
Participation in the environment	x	x	x	Ox-PAQ
Functional disability	x	x	x	BI
Gait functionality	x	x	x	FAC-S.V.
Postural control	x	x	x	PASS-S.V.

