Dynamic trunk balance	x	x	x	TIS-S.V.
Functional goals	x	x	x	GAS

S.V.: Spanish version; NewsQol: Newcastle Stroke-specific Quality of Life Measure; Ox-PAQ: Oxford Participation and Activities Questionnaire; BI: Barthel Index; FAC: Functional Ambulation Categories; PASS: Postural Assessment Scale for Stroke Patients; TIS: Trunk Impairment Scale; GAS: Goal Attainment Scaling.

Secondary variables (Table 2) are as follows:-Level of gait functionality: Measured with the Spanish version of the Functional Ambulation Categories (FAC). The classification ranges between level 0, which indicates that the subject is unable to walk, and level 5, where the person can walk normally. It was validated in the Spanish population by Viosca et al. [39] and has shown to be sensitive for measuring changes in gait in people who have hemiparesis after suffering a Stroke [40].-Postural control: Evaluated through the Spanish version of the Postural Assessment Scale for Stroke Patients (PASS) [41], a specific instrument to evaluate postural control and balance. The total score varies from 0 to 36 points, with the interpretation being that the higher the score, the better the person’s balance. Validated in the Spanish population in 2015 [42].-Dynamic trunk balance: Measured with the Spanish version of the Trunk Impairment Scale (TIS), developed by Verheyden et al., and adapted to the population with Stroke [43]. It consists of two dimensions: dynamic balance in sitting and coordination. The range of scores varies from 0 to 16 points, with higher scores indicating greater trunk control. It is validated for the Spanish population by Cabanas et al. [44].-Functional goals: Assessed with the Goal Attainment Scaling (GAS), which is a 6-point-scale for measuring significant and realistic functional goals, and demonstrated to be a feasible outcome measure among subacute and chronic Stroke patients [45].

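### The Abstract and Section 2.7 swap the roles of FAC and the Barthel Index, so the third primary endpoint is defined in two incompatible ways

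*Protocol article*

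**What the plan says.** The Abstract names three primary and four secondary outcomes: "The primary outcome variables quality of life (NewsQol), participation (Ox-PAQ), and gait functionality (FAC) and the secondary outcome variables functional disability (BI", with PASS, TIS and GAS following as the other secondary outcomes.

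Section 2.7 also lists three primary variables. The first two are again NewsQoL and Ox-PAQ. The third is different: "Functionality: Measured with the modified Barthel Index [37], used to assess the functionality of activities of daily living". The secondary list in the same section then begins: "Secondary variables (Table 2) are as follows:-Level of gait functionality: Measured with the Spanish version of the Functional Ambulation Categories (FAC".

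Table 2 lists all seven outcomes without marking which are primary. Its footnote expands the abbreviations as "BI: Barthel Index; FAC: Functional Ambulation Categories", without the word modified that Section 2.7 uses for the Barthel scale.

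The aim at the end of Section 1 names no instrument, only "improving functionality, participation, and quality of life for people with Stroke". Section 2.3 ties the sample size to one outcome: "In order to detect differences in quality of life in favor of the EG". Section 2.9 sets p < 0.05 for the tests and does not say which outcomes are primary.

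**The concern.** The choice of primary endpoints is the central commitment of a confirmatory trial, and here it is made twice with different content. Both instruments are named and classified in both places, so this is a direct exchange of roles and not an omission that a fuller document would be expected to fill.

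The two scales are not interchangeable. By the article's own description, FAC has six ordered levels from unable to walk to walking normally, and the modified Barthel Index is a 0–100 score of independence in daily activities. A task-specific programme could plausibly move one and not the other. The trial would then support a statement about walking or a statement about daily activities, depending on which section is cited.

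Both measures are taken at baseline, after treatment and at six months. Once results are known, either could be reported as the prespecified primary outcome with a supporting reference to the article. The text leaves that possibility open; it does not state such an intention.

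**Working it through.** **1. The listings side by side**

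| Instrument | Abstract | Section 2.7 | Table 2 |
|---|---|---|---|
| NewsQoL | primary | primary | 1st, no label |
| Ox-PAQ | primary | primary | 2nd, no label |
| Barthel Index | secondary | primary (modified version) | 3rd, no label |
| FAC | primary | secondary | 4th, no label |
| PASS, TIS, GAS | secondary | secondary | 5th–7th, no label |

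Only the Barthel and FAC rows disagree.

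**2. Can another part of the article settle it?**

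- *Aim, Discussion and hypothesis.* These speak of functionality. Section 2.7 gives that heading to the Barthel Index, but the article also uses the word for FAC (gait functionality), and the Abstract and Table 2 call the Barthel outcome functional disability. This leans towards Barthel without deciding the matter.
- *Table 2.* The order matches Section 2.7, but there are no labels.
- *Section 2.9.* No outcome is identified as primary.
- *Sample size.* Inputs from Section 2.3: d = 0.80, α = 0.05, power 90%, 10% loss; Section 2.5 gives 1:1 allocation. With a two-sample t-test (noncentral t):
  - One-sided α: 27 per arm gives power 0.895 and 28 per arm gives 0.905, so 28 per arm, 56 in total. 56 × 1.10 = 61.6, rounded up to **62**, the stated figure.
  - Two-sided α: 34 per arm, 68 in total. 68 × 1.10 = 74.8, rounded up to 75, which is not the stated figure.

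  The calculation uses quality of life only. It is the same whichever functional measure is primary, so it cannot show which was meant.

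**3. What a free choice would cost in type I error**

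Suppose neither outcome is affected by treatment, each is tested two-sided at 0.05, and the better one is reported as primary.

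- Independent outcomes: 1 − 0.95² = 1 − 0.9025 = **0.0975**.
- Correlated outcomes: 1 − P(|Z₁| < 1.96 and |Z₂| < 1.96), with Z₁ and Z₂ bivariate normal with correlation ρ.

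| Assumed ρ | Chance that at least one is significant |
|---|---|
| 0 | 9.75% |
| 0.3 | 9.5% |
| 0.5 | 9.1% |
| 0.7 | 8.3% |
| 0.8 | 7.8% |

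The reference value for one fixed endpoint is 5%. The article gives no correlation between FAC and Barthel, so ρ is an assumption, and the table shows the range.

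**The case against.** The strongest reply is that the evidence is not evenly balanced. Section 2.7 is where outcomes are defined in full, with instrument, range and direction; an abstract is a summary. Table 2 follows the order of Section 2.7, and the aim uses the word that Section 2.7 attaches to the Barthel Index. A reader could reasonably take the Abstract as the slip. The trial is also registered, and the registry entry, which is not at hand, may fix the choice already. All of this stands as an indication of what was probably meant, and it means that undefined would be too strong a word. It does not remove the contradiction, because nothing in the article says that one listing prevails.

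A second reply concerns the 9.75%. It assumes independence, which is unlikely for two functional scales in the same patients. That is right: 9.75% is an upper bound, and the correlated values are more realistic. It also concerns one endpoint only. With three independent primary endpoints each tested at 5%, the chance of at least one false positive is already 1 − 0.95³ = 14.3% with the third one fixed; a free choice between two candidates makes it 1 − 0.95⁴ = 18.5%. Only the difference, about 4.3 percentage points, can be charged to the swap. Testing several primary endpoints is a separate question.

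Third, Section 2.9 offers the same set of parametric and nonparametric tests for all outcomes, so the swap does not leave either scale without a usable test. This stands. What changes is the outcome on which the conclusion rests. The Barthel name and the missing labels in Table 2 are minor points; the finding does not need them.

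**Conclusion.** The concern holds. The Abstract and Section 2.7 give opposite roles to FAC and the Barthel Index, and nothing in the article resolves it. One of three primary endpoints therefore has two incompatible definitions; the other two are consistent.

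The main consequence is that the trial's functional claim, about walking or about daily activities, is not fixed in advance by this document. If the choice were made after seeing the data, the false-positive rate for that endpoint would rise from 5% to between about 7.8% (assumed correlation 0.8) and 9.75% (independence). These figures rest on two-sided tests at 0.05, jointly normal test statistics and an unrestricted choice between the two. They describe a risk that the text leaves open and do not show that such a choice will be made. The sample size is not affected.

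This must be fixed: it concerns what the trial can conclude as a prespecified result, and the correction is easy while comparative data are unseen.

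**What to change.** Before any comparative data are seen:

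1. Name one functional measure as the third primary endpoint. Section 2.7 and the wording of the aim point to the modified Barthel Index, with FAC secondary. If so, correct the Abstract. If FAC was intended, correct Section 2.7 instead and say that the functional aim refers to walking.
2. Check the registry entry against the choice, and align it with a dated explanation if it differs.
3. In the same correction, use one name and version of the Barthel scale throughout, and mark primary and secondary outcomes in Table 2.

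The cost is a correction to the text and possibly a registry update. The sample size of 62, the assessments, their timing and the treatment of participants stay as they are.

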## 1. Introduction

Stroke stands as the foremost cause of physical disability and the second leading cause of mortality among adults in developed nations. This medical condition not only affects the quality of life of individuals but also imposes a significant socio-economic burden on healthcare systems and economies [1,2]. The financial impact is considerable, with the average annual cost per patient in high-income countries estimated to be USD 27,702. Notably, the United States incurs the highest average cost per patient, at USD 59,900, followed by Sweden at USD 52,725 and Spain at USD 41,950 [3]. These figures underscore the critical need for effective prevention, early intervention, and efficient management strategies to reduce both the incidence of Strokes and the financial strain they place on healthcare systems and society at large [1,2,3].

Worldwide, the number of people suffering from Stroke has increased significantly in the recent decades [4]. This increase has been exacerbated by the COVID-19 pandemic, as Stroke is one of the potential complications associated with the virus [5,6]. The prevalence of Stroke notably increases with age, particularly among those over 65 years old. It is estimated that approximately 32.4% of Stroke survivors experience some form of functional dependence six months after the event. This highlights the growing public health challenge and the need for targeted interventions to manage and mitigate the long-term impacts of Stroke [7].

Among the most common long-term effects of Stroke, functional impairments are the leading cause of disability. These impairments can significantly impact balance, leading to gait disturbances and an increased risk of falls. Additionally, they often result in difficulties with handling and performing activities of daily living (ADLs), such as dressing, bathing, and eating [8]. When these alterations continue over time, the negative impact is not only on functionality for ADL performance, but also with the person’s interaction with their environment and participation in social activities [9]. This reduced social engagement can further impact their perceived quality of life [10]. Moreover, the burden of these challenges often extends to family members, who may experience increased stress, social isolation, and decreased life satisfaction [11].

In recent years, a paradigm shift has emerged in the approach to addressing functional dependence among Stroke survivors, guided by the International Classification of Functioning, Disability, and Health (ICF) framework [12,13]. This approach emphasizes the importance of focusing on enhancing functionality and participation rather than solely addressing issues related to body structure and function [14]. This method encourages patients to work towards meaningful goals, which not only aids in their physical recovery but also enhances their overall quality of life by promoting greater independence and social participation [15].

Therefore, it is crucial to emphasize the importance of person-centered approaches in Physical Therapy (PT) interventions to help individuals maximize health, well-being, functionality, quality of life, and participation [16,17]. Person-centered interventions, which focus on functional and meaningful goals, are essential for improving performance. These approaches require the individual’s active involvement in the decision-making process, making them co-responsible for their treatment and subsequent progress [18,19,20]. The interactions between patients and their therapists during the goal-setting process are critical for developing an effective personalized treatment program [18]. This collaborative approach not only enhances the effectiveness of the intervention but also empowers patients, fostering a sense of ownership and motivation in their progress [18,19,20].

The European Stroke Organisation highlights that during motor recovery, patients can optimize their motor, sensory, and cognitive functions by engaging in goal-oriented, repetitive, and progressively challenging task-specific training [7,21,22]. Therefore, PT interventions should also include, among others, the training of functional activities, using task-oriented or task-specific training as an optimal approach strategy for optimizing outcomes [22,23,24]. Including goal-directed approaches and/or task-specific training can enhance PT interventions, leading to improved recovery outcomes for Stroke survivors. This approach has been associated with reduced dependency, lower rates of depression, and increased quality of life and participation [21,22,23,24]. However, more intervention studies with larger sample sizes and detailed methodologies are needed to further validate these findings and refine the implementation strategies [25].

Therefore, the aim of this study is to assess the effectiveness of a PT intervention based on goal-oriented approaches and task-specific training for improving functionality, participation, and quality of life for people with Stroke.

## 2. Materials and Methods

The study protocol follows the Standard Protocol Items: Recommendations for International Trials (SPIRIT) [26].

### 2.1. Study Design

A single-blinded randomized controlled trial will be conducted according to Consolidated Standards of Reporting Trials (CONSORT) guidelines [27]. Figure 1 shows the flow chart of this study.

### 2.2. Ethics Approval and Consent to Participate

This study was approved by the Drug Research Ethics Committee of the Ramon and Cajal University Hospital with code 220/23, and it was registered in the www.clinicaltrials.gov database under identifier NCT06165666.

This RCT complies with the ethical principles of the Declaration of Helsinki [28] and the Spanish Law on Personal Data Protection and Guarantee of Digital Rights [29]. Information sessions about this study will be held for participants where an information sheet will be provided. Informed and written consent will be obtained from all participants before their inclusion into the trial.

### 2.3. Sample Size Calculation

Sample size was calculated using G*Power software 3.1.9.7© (Germany) [30]. In order to detect differences in quality of life in favor of the EG, a large effect size of d = 0.80, an error α = 0.05, and a power of 90% were assumed. Considering a possible loss to follow-up of 10%, the sample size results in 62 participants.

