### 2.9. Statistical Analysis

The Statistical Package for the Social Science software (SPSS^®^ v25) for Mac will be used. An intention-to-treat analysis will be performed. Tests will be carried out with a 95% confidence interval and a statistical significance level of *p* < 0.05. First, descriptive analysis will be performed using means and standard deviations or medians and interquartile ranges otherwise. Normality will be studied through Kolmogorov–Smirnov’s test. For nominal qualitative variables, absolute and relative frequencies will be used. The homogeneity of descriptive and baseline data will be analyzed through Student’s *t*-test for independent samples, Welch’s *t*-test, or the Mann–Whitney U-test. In the case of qualitative variables, Pearson’s χ2 or Fisher’s exact test will be used. Baseline differences will be adjusted through covariate adjustment in regression models. ANCOVA might also be performed to control for baseline differences while comparing the means of the outcome between groups.

To analyze within-group differences between baseline, 6-week, and 6-month assessments, repeated-measures ANOVA or Friedman’s ANOVA will be carried out. To estimate the effect size, partial eta squared will be used. On the other hand, to study the differences between groups, Student’s *t*-test for independent samples, Welch’s *t*-test, or the Mann–Whitney U-test will be carried out. The effect size will be estimated using Cohen’s d or following Grissom’s criteria [47,48,49] in the case of the Mann–Whitney U-test.

Finally, the possible effect of the interaction between descriptive data and independent variables (EG and CG) on the dependent variables will be analyzed through ANCOVA, estimating the effect size using partial eta squared.

Intention-to-treat analysis will be performed in order to reduce, among others, the attrition bias and selection bias that could distort the results. Sensitivity analysis will also be performed in order to address the impact of missing data and ensure the results are as reliable and unbiased as possible.

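### The sample size of 62 fits only a one-sided 5% test; under the two-sided reading of the analysis section, power is about 84% after the planned loss, not 90%

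*Protocol article*

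**What the plan says.** Section 2.3 (Sample Size Calculation) gives the purpose of the calculation as "In order to detect differences in quality of life in favor of the EG". The inputs are "a large effect size of d = 0.80, an error α = 0.05, and a power of 90% were assumed", computed in G*Power. The loss allowance follows: "Considering a possible loss to follow-up of 10%, the sample size results in 62 participants". Section 2.5 sets 1:1 allocation, and the Abstract gives 31 per group. The sidedness of the test is not stated.

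Section 2.9 (Statistical Analysis) says "Tests will be carried out with a 95% confidence interval and a statistical significance level of" p < 0.05. Groups are to be compared by Student's t-test, Welch's t-test or the Mann–Whitney U-test, with no direction named. The section adds that ANCOVA might also be used to control for baseline differences. Neither one-sided nor two-sided testing is mentioned anywhere in the article.

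**The concern.** All the inputs to the calculation are printed, so the figure can be checked directly. Under the usual two-sided 5% test, d = 0.80 with 90% power needs clearly more than 62 participants once 10% loss is allowed for. Either the number is wrong, or it rests on a one-sided test that the analysis section does not carry through.

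The issue is how the result will be read. If quality of life shows no significant difference, readers will judge that against a claimed 10% risk of missing a true d of 0.80. If the real risk is appreciably higher, a null finding will be over-interpreted. Type I error and the validity of the effect estimate are not affected.

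**Working it through.** **Inputs** (Sections 2.3 and 2.5): d = 0.80, α = 0.05, power 90%, 1:1 allocation, 10% loss, stated total 62.

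**Method.** Exact power of the two-sample t-test from the noncentral t distribution, which is what G*Power uses for two means:

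- degrees of freedom = n₁ + n₂ − 2
- noncentrality δ = d × √(n₁n₂ / (n₁ + n₂))
- one-sided power = P(T > t at 1 − α)
- two-sided power = P(|T| > t at 1 − α/2)

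Here T is noncentral t with noncentrality δ.

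**Step 1: reproduce 62 with a one-sided 5% test.**

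- 27 per arm: power 89.5%, not enough.
- 28 per arm: δ = 0.80 × √14 = 2.993, critical value 1.674, power 90.5%. So 56 are needed.
- Loss allowance: 56 × 1.10 = 61.6, rounded up to 62, which is the stated figure. Dividing instead gives 56 / 0.90 = 62.2, rounded up to 63.

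**Step 2: the same inputs with a two-sided 5% test.**

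- 33 per arm: power 89.3%, not enough.
- 34 per arm: δ = 0.80 × √17 = 3.298, critical value 1.997, power 90.2%. So 68 are needed.
- Loss allowance: 68 / 0.90 = 75.6, rounded up to 76; or 68 × 1.10 = 74.8, rounded up to 75. Neither is close to 62.

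**Step 3: two-sided power at d = 0.80 with 62 randomised.** A 10% loss leaves 62 × 0.90 = 55.8, that is 55 or 56 evaluable.

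| Evaluable | Two-sided power | Chance of missing d = 0.80 |
|---|---|---|
| 28 + 27 | 82.9% | 17.1% |
| 28 + 28 | 83.6% | 16.4% |
| 31 + 31 (no loss) | 87.3% | 12.7% |

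If the Mann–Whitney test is used instead, power at 28 per arm is about 81.9%, taking normal data and the asymptotic relative efficiency of 3/π.

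**Step 4: the effect that 62 can detect.** Solving the two-sided power for 90% at 28 per arm gives d = 0.88.

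**Step 5: what baseline adjustment could recover.** Adjusting for the baseline score raises the effective effect to d / √(1 − r²), where r is the correlation between baseline and follow-up. The article gives no r, so the values below are assumptions. All are for 28 per arm and a two-sided 5% test.

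| Assumed r | Effective d | Power |
|---|---|---|
| 0.3 | 0.839 | 86.9% |
| 0.4 | 0.873 | 89.4% |
| 0.5 | 0.924 | 92.4% |

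**The case against.** The strongest defence is that Section 2.3 is consistent on its own terms. It aims to detect a difference in favour of the experimental group, the Discussion states a directional hypothesis, and a one-sided calculation gives exactly 62. The article never says the tests are two-sided, so that part is an inference, and t-tests and Mann–Whitney tests can be run in either direction.

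This explains where 62 came from, but it does not make the plan consistent. The directional wording declares no one-sided test, and the only inferential convention in Section 2.9 is a 95% interval with p < 0.05. A one-sided 5% test corresponds to a 90% two-sided interval. If one-sided testing is intended, Section 2.9 needs correcting; if not, Section 2.3 does.

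Several narrower points do stand:

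- The 83–84% figure assumes the full 10% loss. Without loss it is 87.3%, still short of 90%.
- Multiplying by 1.10 rather than dividing by 0.90 costs one patient (62 against 63). Even 28 + 27 evaluable gives just over 90% one-sided power, so this is immaterial.
- The planned ANOVA and ANCOVA F tests add little evidence on sidedness. Repeated-measures ANOVA is assigned to within-group change, not to the powered comparison. The argument rests on the pairing of the interval with the p-value.
- Baseline-adjusted ANCOVA might restore 90%, but only if the correlation is high enough, and the plan does not commit to it.
- Power of about 84% does not make the trial inadequate. The fault lies in the statement of power.

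**Conclusion.** The concern holds. The stated 62 follows from a one-sided 5% t-test and from no two-sided version of the same inputs. Under the two-sided convention implied by Section 2.9, power for d = 0.80 falls short of the stated 90% by about 6 to 7 percentage points after the planned loss (82.9–83.6%), and by nearly 3 points with complete follow-up (87.3%). Two-sided 90% power would need 68 evaluable, about 76 randomised.

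The conclusion rests on an unadjusted two-sample t-test as the powered comparison, the article's own d, α and loss rate, and the reading of a 95% interval with p < 0.05 as two-sided.

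**What to change.** State the sidedness in Section 2.3 and make Section 2.9 agree with it. The simplest correction keeps N at 62 and rewrites the power statement along these lines: with about 56 evaluable participants (28 per arm), a two-sided 5% t-test has about 84% power for d = 0.80, or 90% power for d = 0.88. This costs one reworded paragraph and a slightly less favourable power figure; no patients are added.

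Three alternatives are also coherent:

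- Commit to a baseline-adjusted ANCOVA as the between-group analysis and base the power on it, with the assumed correlation stated and supported. At 28 per arm, r = 0.5 gives about 92%, but r = 0.4 gives about 89% and r = 0.3 about 87%. This also adds no patients.
- Randomise about 76 to keep two-sided 90% power for d = 0.80, which is 14 more participants.
- Declare and justify a one-sided 5% test in both sections, with a matching confidence interval. N stays at 62, but the evidential standard is weaker than the one Section 2.9 now implies.
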